### Objectives {7}

The overall objective of this mechanistic randomized clinical trial is to use transspinal stimulation over the thoracolumbar enlargement, the spinal location of leg motor circuits, to prime locomotor training and ultimately improve the ability to stand and walk in individuals with chronic incomplete SCI. We hypothesize that non-invasive thoracolumbar transspinal stimulation administered before locomotor training increases neuronal responsiveness over multiple spinal segments, mechanistically reflected by increased responses to motor cortex stimulation, and improved phase-dependent modulation of spinal reflexes during walking. Because transspinal stimulation facilitates anti-gravity neuronal circuits, we further hypothesize that transspinal stimulation delivered while participants stand will augment gains compared to delivery in the supine position. To meet our overall objective, 45 individuals with incomplete SCI will undergo 40 sessions of BWS step training primed with 30 Hz transspinal stimulation. Participants are randomized to receive transspinal stimulation during standing (active or sham) or while supine (active).

Our *specific objective 1* determines whether priming locomotor training with transspinal stimulation strengthens corticomotoneuronal connectivity through posture-dependent corticospinal neuroplasticity, as reflected by increased MEP amplitudes and phase-dependent MEP amplitude modulation during stepping. We hypothesize that active but not sham transspinal stimulation delivered during standing increases MEP amplitudes and improves phase-dependent MEP amplitude modulation during stepping. We further hypothesize that transspinal stimulation delivered while supine increases MEP amplitudes but does not induce phase-dependent MEP amplitude modulation during stepping.

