Our *specific objective 2* determines if priming locomotor training with transspinal stimulation evokes appropriate neuromodulation of spinal locomotor networks, as reflected by restored spinal inhibition, reduced neurophysiological hyperreflexia, and re-established phase-dependent soleus H-reflex modulation during stepping. We hypothesize that active but not sham transspinal stimulation delivered during standing (1) restores soleus H-reflex rate-dependent depression, (2) increases the depth of reciprocal inhibition between ankle extensor and flexor muscles, and (3) improves soleus H-reflex phase-dependent modulation towards a more physiological pattern during stepping. We further hypothesize that rate-dependent soleus H-reflex depression and soleus H-reflex modulation during assisted stepping recovers more in the transspinal-standing group than in the transspinal-supine group.

Our *specific objective 3* determines if priming locomotor training with transspinal stimulation improves the ability to stand and walk. Comparing locomotor electromyography (EMG) activity patterns before and after therapy will measure reorganized motoneuron activity and return of reciprocal activation between antagonistic muscles supporting intralimb and interlimb coordination. We hypothesize that the number of motor modules increases in the transspinal-standing group, and that antagonistic muscles show more reciprocal inhibition during stepping.

Our *specific objective 4* establishes clinically functional gains in motor and autonomic function. Improvements in walking ability are assessed with the 10-m test, 2-min test; improvements in balance ability are assessed with the BESTtest. Improvements in bowel, bladder, and sexual function are assessed with questionnaires. Clinical outcomes will be correlated with neurophysiological outcomes to identify predictors of recovery that can be based both on electrophysiological biomarkers and clinical assessment outcomes.

Upon conclusion, this clinical trial will indicate that priming locomotor training with transspinal stimulation improves the ability to stand and walk by facilitation and better synchronization of spinal locomotor neuronal networks and reflex circuits subserving standing and walking. This finding will support that transspinal stimulation works in parallel and not antagonistic to exercise, and can constitute a new standard of care for people with chronic SCI.

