### Outcomes {12}

#### Primary outcomes

The primary outcomes are neurophysiological biomarkers that accurately probe corticospinal and spinal neuroplasticity (at presynaptic and postsynaptic motoneuron levels):Corticospinal neuronal excitability:

We establish the active MEP threshold that corresponds to the intensity that evokes 10 responses of at least 50 mV following 20 1-ms transcranial magnetic stimulation (TMS) pulses in seated subjects. Then, the soleus MEP recruitment input–output curve is assembled while maintaining small-amplitude contractions. During BWS-assisted stepping, MEPs are recorded at 1.3 times the right soleus MEP active threshold randomly at different phases of the step cycle (divided into 16 equal bins or time windows) based on the signal from the right foot switch. During stepping, MEPs are collected before and after intervention using Lokomat settings matched to the baseline, while an effort is made to record MEPs using Lokomat settings matched to those of the last training session. This establishes changes at matched settings and adaptations during more demanding stepping conditions. MEPs recorded at different stimulation intensities (recruitment curve) are measured as peak-to-peak amplitude and normalized to the soleus maximal M-wave (Mmax) evoked by posterior tibial nerve stimulation to counteract differences in muscle fiber composition across subjects. Stimulation intensities are normalized to the intensity corresponding to the 50% of the MEPmax amplitude, estimated based on the sigmoid function fit to the data. For the participants who have obtainable soleus MEPs at baseline, the main outcomes from this experiment are the MEPmax from the MEP recruitment curves and the MEP amplitude at the mid-stance and mid-swing phases before and after the intervention.2)Spinal neuronal excitability:*2a) Soleus H-reflex rate-dependent (or homosynaptic) depression*: To assess restoration of homosynaptic depression exerted at the synapses between muscle spindle primary Ia afferents and alpha motoneurons, soleus H-reflexes following posterior tibial nerve stimulation at the popliteal fossa with a 1-ms pulse are recorded from seated subjects at different frequencies (1.0, 0.33, 0.2, 0.125, and 0.1 Hz). Homosynaptic depression is greatest at 1.0 Hz and fully recovers at 0.125 and 0.1 Hz [69]. Homosynaptic depression cannot be recorded during stepping because it is abolished by strong spinal inhibitory circuits and efferent activity. The main outcome measure from this neurophysiological biomarker is the soleus H-reflex 1.0/0.1 Hz ratio [70].*2b) Soleus H-reflex depression by antagonistic nerve stimulation*: To examine the restoration of reciprocal inhibitory actions on antagonistic alpha motoneurons, the soleus H-reflex is conditioned by common peroneal nerve (CPN) stimulation at conditioning-test (C-T) intervals of 0, 1, 2, 3 and 4 ms, with subjects seated [71–75]. Reproducible CPN conditioning stimulation is ensured by using a stable, small-amplitude TA M-wave and similar soleus M-wave amplitudes under control and conditioning stimulations. Soleus H-reflexes are measured as peak-to-peak amplitude, accepted for M-waves ranging from 2 to 8% of the maximal M-wave (Mmax), and normalized to the Mmax. The main outcome is the amplitude of the conditioned soleus H-reflex as a percentage of the control H-reflex. The C-T interval for which reciprocal inhibition is present or reciprocal facilitation is the smallest is further investigated during BWS-assisted stepping. The main outcomes are the conditioned H-reflex at rest and during the stance and swing phases of BWS-assisted stepping, which both reflect the amount of reciprocal inhibition.*2c) Control and conditioned soleus H-reflexes during stepping*: During standing with BWS as needed, the soleus H-reflex and M-wave recruitment curves are assembled. Then, each participant steps with the assistance of the Lokomat, and soleus H-reflexes are recorded under control conditions and following CPN conditioning stimulation randomly across 16 equal time bins into which each step cycle is divided based on the signal from the foot switch [75]. The tibial nerve stimulation intensity is adjusted in real-time online to evoke H-reflexes such that their corresponding M-waves are 2–8% of the Mmax evoked 80 ms after the test H-reflex at each bin (Fig. 3). Control and conditioned soleus H-reflexes during stepping are collected before (baseline) and 1–2 days after completion of all 40 intervention sessions at Lokomat settings matched to baseline and the last training session. This approach determines changes at matched settings and reflex adaptation at more demanding settings [76]. During stepping, soleus H-reflexes are measured as peak-to-peak amplitude, accepted for M-waves ranging from 2 to 8% of the Mmax, normalized to the Mmax, and averaged for each bin of the step cycle. The main outcome is the control and conditioned soleus H-reflex amplitude normalized to the Mmax at mid-stance and mid-swing phases.

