## Statistical methods

### Statistical methods for primary and secondary outcomes {20a}

For each dependent variable (primary and/or secondary outcome), descriptive statistics including frequencies and percentages for categorical variables and means and percentile distributions for continuous variables to examine the distribution of outcomes and describe the study population are performed.

We will group each dependent variable based on the time of testing (before and after the intervention) and the subject group (2 experimental, 1 sham). A two-way mixed analysis of variance (ANOVA) along with Bonferroni post hoc* t-*tests [93] at 2 3 levels (2: time, 3: groups) to test the main and interaction effects among subject groups and time will be performed separately for each outcome. Furthermore, repeated measures analysis of covariance (ANCOVA) will be performed for each outcome separately with gender, age, level of SCI, and clinically evaluated baseline walking function as separate covariates. Outcomes will not be analyzed based on SCI severity because the ISNCSCI scale does not correlate with improvements in walking ability [3], while age is considered one of the predictors of ambulation in SCI [94].

Mixed regression methods and analysis of slope and threshold of correlation will be used to establish the relationship between the ability to stand and walk, quality of life, and changes in primary outcomes (neurophysiological biomarkers). We will use an identity or log link based on the data distribution.

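### The modulation hypotheses of Objectives 1 and 2 are analysed only through separate mid-stance and mid-swing amplitudes, with no phase term or stance-swing contrast

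*Protocol article*

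**What the plan says.** **Objectives {7}.** Objective 1 names two quantities for the MEP, "as reflected by increased MEP amplitudes and phase-dependent MEP amplitude modulation during stepping", and then separates them: supine stimulation is predicted to be a treatment that "increases MEP amplitudes but does not induce phase-dependent MEP amplitude modulation during stepping". Objective 2 predicts, among other things, that active standing stimulation "improves soleus H-reflex phase-dependent modulation towards a more physiological pattern during stepping", and that H-reflex modulation recovers more with standing than with supine stimulation.

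**Primary outcomes.** During stepping, responses are recorded across 16 bins of the step cycle. H-reflexes are "normalized to the Mmax, and averaged for each bin of the step cycle". The main outcomes are then two points of the cycle: for MEPs, "the MEP amplitude at the mid-stance and mid-swing phases before and after the intervention" (with MEPmax from the recruitment curve), and for reflexes, "The main outcome is the control and conditioned soleus H-reflex amplitude normalized to the Mmax at mid-stance and mid-swing phases". Outcome 2b separately declares the conditioned H-reflex in stance and in swing as a measure of reciprocal inhibition.

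**Statistical methods {20a}.** The test is a mixed ANOVA with time (2 levels) and group (3 levels), which "will be performed separately for each outcome". The ANCOVA versions add gender, age, injury level and baseline walking function. The mixed regression relates function and quality of life to changes in the biomarkers. Phase or bin appears in none of these.

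**The concern.** Modulation is a difference between phases of the step cycle. A time x group interaction for mid-stance amplitude asks whether the arms changed differently in stance, and the same test for mid-swing asks this for swing. Neither asks whether the difference between the phases changed. Significance in one phase but not the other does not test that difference either.

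Objective 1 is the most exposed. Its supine hypothesis is that amplitude rises and modulation does not appear. That pattern and a true modulation effect can give the same set of significant phase tests. A general rise or fall in excitability could then be reported as restored modulation in a trial that presents itself as mechanistic.

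**Working it through.** **1. The plan's own figure.** The stepping H-reflex calculation uses mid-stance amplitude only: 13.67 / 17.4 = 0.786, stated as 0.79. With a one-way ANOVA, 3 groups, alpha 0.05 and noncentrality N f², entering f = 0.79 gives power 0.78 at N = 18 and 0.85 at N = 21. The stated total of 21 is reproduced. It is the size for one amplitude in one phase, not for a difference between phases. (Whether a pre-post d may be entered as a between-group f is a separate question.)

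**2. Set-up.** With two time points, the time x group interaction is a one-way ANOVA on change scores.
- From the article: 3 arms, 15 per arm, alpha 0.05; 12 per arm after the projected 20% dropout.
- Assumed: change scores with SD 1 in each phase, one arm differing from the other two, and correlation rho between a participant's stance and swing changes. The article does not give rho.
- Noncentrality when one arm is shifted by delta: n x (2/3) x delta² / variance.
- Variance of the stance-minus-swing change: 2(1 - rho).

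**3. Uniform shift, +1 SD in both phases (modulation unchanged).** For each phase test, noncentrality is 15 x 2/3 = 10 on 2 and 42 degrees of freedom, so power is 0.785. The contrast has delta = 0 and rejects at its nominal 5%. Simulated probability that at least one phase test is significant:

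| rho | 15 per arm | 12 per arm | contrast |
|---|---|---|---|
| 0.3 | 0.93 | 0.86 | 0.05 |
| 0.5 | 0.91 | 0.83 | 0.05 |
| 0.6 | 0.90 | 0.81 | 0.05 |

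**4. Swing-only shift, -1 SD (modulation changes by 1 SD).** The mid-swing test again has noncentrality 10 and power 0.785. The contrast has noncentrality 10 / [2(1 - rho)]:

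| rho | noncentrality | contrast power | mid-swing test |
|---|---|---|---|
| 0 | 5.0 | 0.474 | 0.785 |
| 0.3 | 7.1 | 0.631 | 0.785 |
| 0.5 | 10.0 | 0.785 | 0.785 |
| 0.6 | 12.5 | 0.872 | 0.785 |

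The two are equal at rho = 0.5, where 2(1 - rho) = 1. Below that the mid-swing test has more power.

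**5. Opposite shifts, +0.5 / -0.5 SD (also a 1-SD modulation change).** Contrast power is as in step 4, so 63-87% for rho 0.3-0.6. Each phase test has noncentrality 2.5 and power 0.26, and at least one is significant in 47-48% of simulated trials.

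The result in step 3 follows from the structure of the tests. The power ranking in steps 4 and 5 reverses with the pattern of change and with rho.

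**The case against.** **The article condenses a fuller plan.** The analysis plan is not shown, and an index derived from recorded bins is the kind of detail it might hold. The article does not say in so many words that stance and swing are separate outcomes, and its statement that there are no additional analyses stands under the heading on subgroup-type analyses, so it does not clearly bar a contrast. This limits how hard the point can be pressed but does not remove it. The outcomes and both ANOVA factors are stated, and reading the two phases as one outcome does not help, because the 2 x 3 model has no phase term.

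**A fall in swing may itself be the modulation.** The Background describes partial return of H-reflex depression in swing as the commonest change with step training, and mid-swing amplitude captures that directly, in some cases with more power than a contrast. This stands as regards power. It does not show that stance stayed put: an equal fall in stance would give the same swing result.

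**No decision rule equates a significant phase test with modulation.** That is correct. The 90-93% is how often the planned tests would give a signal open to that reading, not the error rate of a stated rule.

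**Stronger readings a reader might infer.**
- That the planned tests say nothing about modulation. Two directional results, such as stance unchanged and swing reduced, do bear on it, though indirectly.
- That Objective 2 also sets reflex size against modulation. Only Objective 1 draws that contrast.
- That the phase amplitudes should give way to the contrast. For the conditioned reflex, this would remove the stepping measure of reciprocal inhibition that outcome 2b declares.

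**Conclusion.** The point holds for MEPs and control soleus H-reflexes during stepping: hypotheses about modulation are stated, and the stated analysis contains no test of it. It matters most for Objective 1's supine hypothesis. The locomotor EMG listed under Other outcomes does not fill the gap, because it is a different measurement.

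The supported size is the loss of specificity: about 90-93% against 5% for a uniform 1-SD shift with 15 per arm, or 81-86% against 5% with 12. These figures rest on unit-SD normal changes, one differing arm and an assumed rho of 0.3-0.6. The MEP analysis is limited to participants with obtainable soleus MEPs at baseline, so its numbers may be smaller. It would be wrong to infer that the contrast is generally more powerful; steps 4 and 5 of the working point in opposite directions at low rho.

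**What to change.** For the modulation hypotheses on the MEP and the control soleus H-reflex, define one measure per participant and visit: mid-stance minus mid-swing amplitude (% Mmax), at Lokomat settings matched to baseline. Analyse it by time x group. Equivalently, add phase as a within-subject factor and test group x time x phase. State that any claim about modulation rests on that test, and fix this before group allocations are unblinded for the comparisons.

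Keep the separate mid-stance and mid-swing amplitudes as declared, including the conditioned H-reflex in stance and swing for reciprocal inhibition.

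Cost: wording plus one derived outcome for each of the two responses, with no new recordings. The downside is lower power than the mid-swing test if only swing changes and the between-phase correlation is below about 0.5. That correlation should be estimated from the group's earlier stepping data, if available, before any power is quoted for the contrast.

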
**Fig. 3 Fig3:**
[figure not shown]
Arrangement of stimuli during stepping. EMG channel, along with reflex and conditioning stimuli are shown as detected in LabVIEW data acquisition software. Test and/or conditioning stimulation (that can be directed to the primary motor cortex, skin, or peripheral nerve as single pulses or pulse trains at variable frequencies) are indicated for an interval that can be adjusted based on the experimental protocol. Through foot switches (not shown), we determine the exact phase that stimulation occurs, i.e., the exact bin. Stimulation is delivered randomly across the 16 bins that make up each step cycle

#### Secondary outcomes

The secondary outcomes include the International Standards for Neurological Classification of SCI (ISNCSCI) sensory and motor scores, temperature sensation, proprioceptive sensation, ability to stand and walk, and autonomic function. Standing and balance ability is evaluated with the Berg Balance Scale [77, 78] and BEST tests [79]. Walking capacity is tested with the 2-min and 10-m walking tests [80]. A combination of validated questionnaires related to bladder, bowel, and sexual function are used to assess autonomic function [81–87].

#### Other outcomes

Other outcomes include the recordings of the muscle activation profiles. Locomotor EMG activity is collected to establish changes in the phase-dependent amplitude modulation of muscle activity at bilateral soleus, tibialis anterior, medial gastrocnemius, peroneus longus, medial hamstrings, adductor gracilis, vastus lateralis, and vastus medialis muscles. EMG signals are full wave rectified, band-pass filtered, normalized to the homonymous maximal EMG, plotted against the step cycle, and grouped based on the time of testing and intervention study group. Outcomes are changes in intralimb and interlimb coordination [27].

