The soleus H-reflex amplitude during assisted stepping in 11 persons with motor incomplete SCI (AIS C-D) recorded from the right leg was compared before and after locomotor training [26]. Based on the amplitude of the soleus H-reflex at mid-stance before and after training (difference in means of pre versus post: 13.67, pooled standard deviation: 17.4), the effect size was 0.79. To predict sample size at a power of 0.80 at α = 0.05 using a one-way ANOVA across 3 groups, 21 total subjects are needed. We will enroll 45 subjects, so we will be adequately powered even if subjects drop out at a higher than expected 20% rate.

Limb coordination relies on the strength of reciprocal inhibition between antagonistic muscles. We used data from a study performed by our group that examined short-latency inhibition from ankle flexor afferents onto ankle extensor motoneurons at rest in 13 persons with AIS C-D SCI before and after locomotor training [28]. Based on the amplitude of the conditioned H-reflex at the conditioning-test interval of 2 ms before and after training (difference in mean of pre versus post: 15.04, pooled standard deviation: 17.21), the effect size was 0.874. To predict sample size at a power of 0.80 at α = 0.05 using a one-way ANOVA across 3 groups, 18 total subjects are needed. We will enroll 45 subjects, so we will be adequately powered even if subjects drop out at a higher than expected 20% rate. Please note that the established power was based on data from SCI subjects who received either transspinal stimulation or locomotor training separately and not combined.

*Aim 3*: Determine if priming locomotor training with high-frequency transspinal stimulation improves limb coordination and the ability to stand and walk. These are secondary measures, and the study is not powered based on these outcomes.

Collectively, an average of 6 to 8 subjects per group is needed to establish significant differences for primary outcomes before and after transspinal stimulation or locomotor training. By enrolling 15 participants per group, the study will be robustly over-powered to detect these differences despite a projected possible 20% dropout rate, sporadic missing data values, or lower-than-expected observed effect sizes.

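### The locomotor EMG steps are listed with rectification before band-pass filtering; followed literally with a usual EMG pass band, that order removes the step-cycle profile it is meant to show

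*Protocol article*

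**What the plan says.** The Other outcomes part of Outcomes {12} gives the purpose of the recordings: "Locomotor EMG activity is collected to establish changes in the phase-dependent amplitude modulation of muscle activity", in eight muscles on each side. It then lists the processing: "EMG signals are full wave rectified, band-pass filtered, normalized to the homonymous maximal EMG, plotted against the step cycle", after which records are grouped by time of testing and study arm. No pass band, filter type or smoothing step is given. The outcomes are named as changes in coordination within and between limbs, with a reference to a cited study.

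Specific objective 3 in Objectives {7} relies on locomotor EMG compared before and after therapy, and adds: "We hypothesize that the number of motor modules increases in the transspinal-standing group, and that antagonistic muscles show more reciprocal inhibition during stepping". No method for extracting motor modules is named. Participant timeline {13} also repeats locomotor EMG at visits t15 and t30. On the matching aim, Sample size {14} says: "These are secondary measures, and the study is not powered based on these outcomes".

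**The concern.** The aim is to see how muscle activity rises and falls over the step cycle. Raw surface EMG swings around zero, and rectifying it turns burst size into a local mean level. That level changes slowly, at the step rate and its first few multiples. A band-pass filter applied after rectification discards the mean and, with a usual EMG lower cut-off, those slow components too. What remains is a signal of both signs whose phase averages lie close to zero. Scaling by a maximal EMG value cannot bring the profile back.

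If the list were followed literally, a real recovery of modulation in any arm could look like almost none, and a null EMG result could come from the processing alone. Negative values would also be unusable in a non-negative decomposition into motor modules, if that is the method chosen (an assumption).

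**Working it through.** The plan gives no figure to reproduce, so the check is algebra followed by simulation. The documents supply the order of steps and a 16-bin step cycle (stated for the MEP and H-reflex recordings, not for EMG). Everything else below is an assumption.

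**1. Where the information sits.** Write the EMG as x(t) = a(φ)·n(t), with a the amplitude at step phase φ and n a zero-mean Gaussian carrier. Then the expected value of |x| is c·a(φ), with c = √(2/π) = 0.798. Because a repeats every step, it has components only at 0 Hz and at multiples of the step rate 1/T. With T = 2 s these lie at 0, 0.5, 1.0, 1.5 Hz and so on. A band-pass filter has no gain at 0 Hz, so the mean goes whatever the lower cut-off. Multiples of the step rate below that cut-off go as well.

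**2. Size of the loss.** Simulation: sampling at 2000 Hz, 40 steps of 2 s, unit-variance carrier of 20–450 Hz, a(φ) = 0.1 + exp(−½((φ − 0.35)/0.12)²), second-order zero-phase Butterworth filter, signed averages in 16 bins. Check on the rectified signal: mean a ≈ 0.1 + 0.12·√(2π) = 0.401, and 0.798 × 0.401 = 0.320, against 0.3197 simulated. Share kept is the bin range divided by the rectified-only range of 0.7904; r is the correlation of the bin profile with the true envelope.

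| Processing | Mean | Negative samples | Bin range | Share kept | r |
|---|---|---|---|---|---|
| Rectify only | 0.3197 | 0% | 0.7904 | 100% | 1.000 |
| Band-pass 20–450 Hz, then rectify | 0.2934 | 0% | 0.7246 | 91.7% | 1.000 |
| Rectify, then 0.1–10 Hz | 0.0028 | 63% | 0.7907 | 100% | 1.000 |
| Rectify, then 0.5–10 Hz | 0.0003 | 68% | 0.5115 | 64.7% | 0.957 |
| Rectify, then 1–10 Hz | 0.0000 | 51% | 0.2083 | 26.4% | 0.555 |
| Rectify, then 5–450 Hz | 0.0000 | 57% | 0.0070 | 0.9% | 0.109 |
| Rectify, then 10–450 Hz | 0.0000 | 57% | 0.0051 | 0.6% | 0.041 |
| Rectify, then 20–450 Hz | 0.0000 | 57% | 0.0044 | 0.6% | 0.006 |
| Rectify, then 30–500 Hz | 0.0000 | 57% | 0.0040 | 0.5% | −0.023 |

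The algebra explains the fall. For this envelope the k-th multiple of the step rate has relative size exp(−2π²·0.12²·k²) = exp(−0.284k²): 0.75 at 0.5 Hz (k = 1), 0.32 at 1 Hz (k = 2) and 0.01 at 2 Hz (k = 4). Almost nothing is left to pass a 5 Hz lower cut-off.

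**3. What it would do to a before–after comparison.** A second simulation used 60 steps of 2 s, 60% stance and a 20–450 Hz carrier. Amplitude ran from 20 (swing) to 30 (mid-stance) units before therapy, and from 5 to 60 after. Band-pass then rectify gives a bin depth of 7.48 before and 39.04 after, a ratio of 39.04/7.48 = 5.2. In the listed order the share of that depth kept, before/after, is:

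- 1 Hz lower cut-off: 23.8% / 21.1%
- 5 Hz: 3.2% / 1.1%
- 10 Hz: 2.0% / 0.7%
- 20 Hz: 1.7% / 0.5%
- 30 Hz: 1.3% / 0.3%

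At 20 Hz this is 0.017 × 7.48 = 0.13 units before and 0.005 × 39.04 = 0.20 after, so the fivefold gain is no longer visible. Negative samples are 56–58% and the overall mean is 0.00–0.01 units.

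**4. Whether a later step would rescue it.** After rectifying and filtering at 20–450 Hz, the RMS in each bin correlates 0.9997 with the envelope, and a second rectification gives 1.000 for lower cut-offs of 5 to 30 Hz. For the low-frequency bands a second rectification does not help: r is 0.70 at 0.1–10 Hz, 0.78 at 0.5–10 Hz and 0.80 at 1–10 Hz.

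**The case against.** The sentence is a condensed comma list in a journal article. It has no numbered steps and no explicit word of order, and filter settings are commonly left to the full protocol. The laboratory may well filter first and rectify second. That stands as a limit: the text does not prove that any recording has been processed in the listed order. It does not remove the point, because the remaining items (normalise, plot, group) are in working order, so the natural reading is a sequence. A missing cut-off is article brevity; a stated order that defeats its own purpose is not.

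It can also be said that the loss depends on a pass band nobody has stated, and that the near-zero result comes from averaging a signed signal in bins. Both are correct. With a lower cut-off at or below the assumed 0.5 Hz step rate the shape largely survives, and an RMS step after a usual EMG band restores it. The article neither states nor excludes such a step. Only the loss of the mean, with the negative values that follow, holds for every lower cut-off.

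A reader might go further and infer that the objective 3 results will be wrong, or that objective 3 rests on EMG alone. The documents support neither. Standing and walking are measured by the Berg Balance Scale, BEST test, 2-min and 10-m tests (Secondary outcomes), and reciprocal inhibition is measured separately by conditioned H-reflexes at rest and during stepping (Primary outcomes, 2b and 2c).

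**Conclusion.** The point holds as a minor correction. The listed order, taken literally with a usual surface-EMG band, keeps about 0.3 to 3% of the bin-averaged modulation depth and so defeats the purpose stated in the same paragraph. This size rests on an assumed lower cut-off of 5 Hz or more, a 2-s step, smooth simulated bursts, signed averaging in 16 bins and no later amplitude step.

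What is affected is the EMG part of objective 3: activation profiles, coordination within and between limbs and, if a non-negative decomposition is used, the motor-module count. The primary MEP and H-reflex measures are peak-to-peak amplitudes and are untouched, as are the clinical tests. The EMG measures sit under Other outcomes, and the study is not powered on them.

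**What to change.** Reword the processing sentence so that the raw EMG is band-pass filtered first and full-wave rectified second, with a low-pass filter added where a linear envelope is needed; it is then scaled to the same muscle's maximal EMG and plotted over the step cycle. The numerical pass band may stay in the full protocol or analysis plan. Apply the same rule to the baseline, t15, t30 and final recordings, and settle it before allocation is revealed for the between-group tests. If any recordings were already processed in the listed order, rerun them from raw EMG where that was kept.

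The cost is one sentence and, at most, one rerun of the processing. No new recordings or visits are needed.
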